## Abstract

**Background:**

Community-acquired pneumonia, especially severe community-acquired pneumonia (SCAP), remains the leading cause of death in the world. Despite advances in antimicrobial therapy, the mortality rates due to SCAP have not decreased significantly since antibiotics became routinely available. Traditional Chinese medicine (TCM) has been used for treating pneumonia for thousands of years. It is popular and widely practiced in Asia. In recent decades, evidence from both clinicians and patients suggests that TCM has some beneficial effect on SCAP. Thus, this study aims to compare the efficacy of a combination of a conventional drug and TCM to the conventional drug alone, to provide a scientific basis for clinical decisions.

**Methods/design:**

A prospective, multi-center, single-blinded, double-dummy, and randomized controlled clinical trial is being conducted to test the therapeutic effects of a combination of conventional medicine and TCM versus conventional medicine in the treatment of SCAP. A total of 198 patients will be enrolled in this study, with 99 in each treatment group (combination group or conventional medicine group). The TCM will be administered twice daily for 28 days. All patients will be followed for 3 months. The primary outcome measure is treatment failure, which is defined as clinical deterioration. Secondary outcome measures are time to clinical stability, length of hospital stay, in-hospital mortality, SOFA questionnaire, quality of life and cost of treatment.

**Discussion:**

It is hypothesized that the combination of a conventional drug and TCM will reduce treatment failure, time to clinical stability, length hospital of stays, and in-hospital mortality, and improve the quality of life of SCAP patients.

**Trial registration:**

ClinicalTrials.gov, NCT03185923. Registered on 20 June 2017.

**Electronic supplementary material:**

The online version of this article (10.1186/s13063-018-3005-9) contains supplementary material, which is available to authorized users.

## Background

Community-acquired pneumonia (CAP) is the leading cause of death due to infection worldwide [1, 2]. Despite advances in antibiotic treatment, mortality among hospitalized patients with CAP is still high, especially in those with severe pneumonia [3] and in those who experience treatment failure [4]. Patients with treatment failure, which is defined as clinical deterioration, may have higher rates of mortality compared with those who do not experience treatment failure [4], so it is possible to use treatment failure as a surrogate parameter for mortality. In patients with CAP, an excessive host inflammatory response is associated with treatment failure during intensive care unit admission and with mortality [5, 6].

Many different organizations have worked to improve the care of patients with CAP. Such efforts are warranted, because CAP, especially severe community-acquired pneumonia (SCAP), remains the leading cause of death globally. Despite advances in antimicrobial therapy, mortality rates due to SCAP have not decreased significantly since penicillin became routinely available.

Traditional Chinese medicine (TCM) has been used for thousands of years for treating pneumonia. It is popular and widely practiced in many countries around the world. In recent decades, evidence from both clinicians and patients suggests that TCM has some beneficial effect on SCAP [7, 8].

At present, many complementary therapies are offered for patients with SCAP. Moreover, it is not very clear whether TCM is a suitable therapy for SCAP. Thus, this study aims to compare the efficacy of a combination of a conventional drug and TCM to the conventional drug alone, to provide a basis for clinical decisions.

This multi-center randomized controlled trial will compare the efficacy of two therapies for patients with SCAP. In total, 198 subjects will be randomly assigned to one of the therapies (conventional drug alone or the combination of the conventional drug and TCM) for 28 days of treatment. After the treatment period, the subjects both two arms will be followed up for 3 months. The primary outcome will be treatment failure. The secondary outcomes are time to clinical stability, length of hospital stay, in-hospital mortality, sequential organ failure assessment (SOFA), quality of life (CAP-PRO), and health economics.

## Methods/design

### Objective and design

This is a multicenter, pragmatic, randomized, controlled trial to evaluate the effectiveness of integrated TCM treatment for SCAP patients. A total of 198 patients will be recruited and randomly assigned to one of the two treatment groups. After the 28 days of treatment, they will be followed for another 3 months. The primary outcome (treatment failure) and secondary outcomes (time to clinical stability, length hospital of stay, in-hospital mortality, SOFA questionnaire, quality of life, and health economics) will be assessed at different points within the trial.

The study has been approved after meeting conditions imposed by the ethical research committee of the First Affiliated Hospital of Henan University of Traditional Chinese Medicine (identifier 2017HL-002-01). This trial adheres to the Declaration of Helsinki and was registered at ClinicalTrials.gov (NCT03185923) on 20 June 2017. The protocol follows the recommendations of the SPIRIT initiative (Additional file 1) [9], and the trial results will be reported according to the latest version of the CONSORT statement [10].

### Study setting and participants

All adult patients with SCAP at respiratory departments in 11 tertiary-care hospitals will be screened and enrolled. Eligible patients will be asked for their informed consent and then centrally randomized to either the integrated traditional Chinese and conventional medicine group or to the conventional medicine group in a ratio of 1:1. All medications will be taken orally for 28 days. If the patient is not able to give informed consent at the time of hospitalization due to the severity of their CAP, informed consent from their next of kin and an independent physician will be obtained. In these cases, informed consent from the patient will be obtained as soon as possible. Patient recruitment started in July 2017 and is planned to be completed in December 2019.

To be included, patients must be aged between 18 years and 80 years, and must meet the criteria for SCAP (defined with the modified American Thoracic Society criteria) [11] and the criteria for TCM syndromes. TCM syndrome differentiation relates to pathological changes: phlegm-heat obstruction in the lung, pulmonary stagnation of phlegm, pathogenic heat trapped in the pericardium, or pathogenic depression.

The following patients are excluded:Pregnant and lactating womenPatients with trauma, hematologic malignancies, various solid tumors, obstetric complications, aspiration pneumonia, fungal pneumonia, HIV-related pneumocystis carinii pneumonia, tuberculosis, bronchiectasis with infection and a pulmonary abscess, dementia, mental illness, neuromuscular disorders affecting the respiratory motor function, severe cardiovascular disease, severe liver disease, or kidney diseasePatients who are unwilling to cooperatePatients who were discharged from hospital within 2 days or require an operationPatients with severe immunosuppression (due to HIV infection, immunosuppressive conditions, or medication).Patients who have participated in other clinical studies in the past 4 weeksPatients unwilling to sign the informed consent.

### Randomization

Participants who meet the inclusion criteria and sign the informed consent form will be allocated to a group (Fig. 1). A stratified and block randomization design has been adopted. There are two groups and the distribution ratio is 1:1. The block size is six. Patients are stratified at the time of study entry by study center. Allocation is based on random numbers from 1 to 198 generated by SAS 9.2 and saved in a sealed envelope by an independent clinical statistician. In a clinical emergency, the individual’s randomization code and group allocation can be quickly identified by checking the envelope. The randomization design is provided by the Jiangsu Famous Medical Technology Co., Ltd.

**Fig. 1 Fig1:**
[figure not shown]
Flow chart of study design. TCM traditional Chinese medicine

### Study protocol

All patients are being treated according to current CAP guidelines [11]. Antibiotic therapy guided by an established procalcitonin algorithm is encouraged. The time of discharge is not determined by the study investigators, but chosen by the treating physician team.

For the combination of conventional medicine and TCM, patients will be given herbal interventions based on TCM syndrome patterns: *qing-fei jie-du hua-tan* granules (Sanjiu Medical & Pharmaceutical Co., Ltd.) for phlegm-heat obstruction in the lung, *zao-shi hua-tan xie-fei* granules for pulmonary stagnation of phlegm, *qing-xin kai-qiao* granules for pathogenic heat trapped in the pericardium, *shenmai* injections for yin exhausted syndrome, and *shenfu* injections for yang exhausted syndrome. The herbal interventions are recognized as a holistic intervention. The TCM granules are compound preparations of Chinese herbs and the main components are listed in Table 1. Each type of granule comes in bags, which are produced and packed by Sanjiu Medical & Pharmaceutical Co., Ltd. Test results of drug quality were consistent with the required quality standards. Each type of granule will be given orally, two bags each time, twice a day for 28 days.

**Table 1 Tab1:** Main components of traditional Chinese medicine

Chinese name	Latin name	Amount (g)
*Qing-fei jie-du hua-tan* granule for phlegm-heat obstruction in the lung		
*Huang qin*	Radix scutellariae baicalensis	9
*Zhe bei mu*	Bulbus fritillariae thunbergii	9
*Gua lou*	Fructus et semen trichosanthis kirilowii	20
*Xi yang shen*	Radix panacis quinquefolii	6
*Zao-shi hua-tan xie-fei* granule for pulmonary stagnation of phlegm		
*Fa ban xia*	Prepared pinellia tuber	12
*Hou pu*	Cortex magnoliae officinalis	9
*Fu ling*	Poria	15
*Zi su zi*	Fructus perillae argutae	9
*Qing-xin kai-qiao* granule for pathogenic heat trapped i the pericardium		
*Shui niu jiao*	Cornu bubali	30
*Sheng di huang*	Radix rehmanniae	15
*Xuan shen*	Radix scrophulariae	12
*Mai dong*	Radix ophiopogonis japonici	12

For the conventional medicine group, patients will be given placebo herbal interventions according to the TCM syndrome.

### Data collection

Baseline data are collected by electronic case report forms compliant with good clinical practice. They include date and time of randomization, date of birth, sex, and medical history (dyspnea, cough, smoking history in pack-years, current smoking status in packs per day, relevant comorbidities, degree of autonomy at home, clinical items of pneumonia, pneumonia severity index, extent of pneumonia, and presence of underlying chronic obstructive pulmonary disease as assessed by patient history and medical documents).

In both groups, hospitalized patients are reassessed clinically every 24 h (including vital signs). Details of doses of all prescribed antimicrobials during the study period are recorded. In hospitalized patients, hospital discharge is recommended if oral intake is feasible, vital signs have been stable for ≥24 h, and there is no evidence of an acute serious comorbidity that necessitates hospitalization. On days 1, 4, 7, 14, and 28 the patient will be asked to complete a short questionnaire on their respiratory symptoms.

### Follow-up

Structured follow-up telephone interviews for secondary outcomes after discharge are performed on days 30, 60, and 90 (Fig. 2). If the patient cannot be contacted or cannot give sufficient information, their primary-care physician will be interviewed. Follow-up items include assessment of adverse events (such as infections, recurrent pneumonia, and re-hospitalization), and the standardized questionnaire on respiratory symptoms.

**Fig. 2 Fig2:**
[figure not shown]
Schedule of enrolment, interventions and assessments (as per SPIRIT [9]). CAP community-acquired pneumonia, PSI, pneumonia severity index, TCM traditional Chinese medicine

### Outcome measures

#### Primary outcome measure

The primary endpoint is treatment failure, which includes treatment failure that occurred early or late. Early treatment failure is defined as clinical deterioration within 72 h of treatment (including shock, need for invasive mechanical ventilation not present at baseline, or death). Late treatment failure is defined as radiographic progression (increase of ≥50% of pulmonary infiltrates compared with baseline), persistence of severe respiratory failure (ratio of PaO_2_ to fraction of inspired oxygen < 200 mmHg with respiratory rate ≥ 30 breaths/min in patients not intubated), need for invasive mechanical ventilation not present at baseline, or death 72 h after treatment initiation. These criteria have been used previously with modifications [12].

#### Secondary outcome measures

We will consider the following secondary endpoints.

##### Time to clinical stability

Clinical stability occurs when [11]: temperature ≤37.2 °C, heart rate ≤100 beats/min, systolic blood pressure ≥90 mmHg, and arterial oxygen tension ≥60 mmHg if the patient is not receiving supplemental oxygen. In patients receiving oxygen therapy at home, stability is achieved when their oxygen needs were the same as before admission.

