##### Length of hospital stay

The time to the earliest possible hospital discharge (days) is based on objective criteria (able to take food, liquids, and drugs orally; vital signs stable for > 24 h; recovered from CAP-related worsening of mental status; and no evidence of an acute serious CAP-related comorbidity that necessitates hospitalization). This endpoint will minimize any potential bias due to extended hospitalization for non-disease-specific reasons (a request from the patient or their relatives, lack of adequate home care, inability to transfer to a nursing home, or lack of assurance about compliance with treatment) [13].

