#### Sample size considerations

This study is designed to show the superiority of the TCM group compared to placebo treatment. Our primary hypothesis is that adjunct TCM treatment in patients with SCAP will result in reduced treatment failure compared to the placebo. To estimate the frequency of our primary endpoint, we used data for SCAP patients from completed studies [12]. Based on these previous trials, we assumed a treatment failure rate of 30% in the placebo group and 10% in the adjunct TCM group over 28 days. Thus, a sample size of 198 patients is needed to achieve a statistical power of 90% (two-sided type-1 error of 5% in both scenarios). We intend to recruit 198 study patients from July 2017 to December 2019.

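### As printed, time to clinical stability sets no oxygenation test for patients newly on oxygen or ventilation, so stability can coincide with treatment failure

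*Protocol article*

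**What the plan says.** Under Time to clinical stability, the first secondary endpoint listed, the protocol article sets three vital-sign limits, "temperature ≤37.2 °C, heart rate ≤100 beats/min, systolic blood pressure ≥90 mmHg", and one oxygen limit, "arterial oxygen tension ≥60 mmHg if the patient is not receiving supplemental oxygen". One further sentence follows: "In patients receiving oxygen therapy at home, stability is achieved when their oxygen needs were the same as before admission". Respiratory rate does not appear, and nothing is said about a patient who had no oxygen at home and is now receiving it in hospital.

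Under Primary outcome measure, late treatment failure includes severe respiratory failure that persists, defined by a ratio of PaO2 to "fraction of inspired oxygen < 200 mmHg with respiratory rate ≥ 30 breaths/min in patients not intubated". A separate component, listed for both early and late failure, is "need for invasive mechanical ventilation not present at baseline".

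**The concern.** The oxygen limit is written as a condition. If the patient is off oxygen, PaO2 must reach 60 mmHg. If the patient has newly been put on oxygen, the condition is not triggered and no other test takes its place. What remains is control of fever, pulse and blood pressure.

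The rule then behaves oddly. A home-oxygen patient who needs more than before admission is not stable, while a patient with no previous oxygen who now needs a high inspired fraction can be. The same patient could also be recorded as recovered on the first-listed secondary endpoint and, over the same days, as failed on the primary endpoint.

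The Discussion describes the population as the highest pneumonia severity class and in need of hospital care, so newly started oxygen is unlikely to be a rare case. Eleven hospitals will apply the rule. If they read the clause differently, the endpoint will not mean the same thing across sites.

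**Working it through.** No stated figure bears on this point, so the check sets the two definitions side by side and runs example patients through both.

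**The two readings.** Let V mean that all three vital-sign limits are met. For a patient without home oxygen:

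- Reading A (literal condition): stable = V and (on oxygen, or PaO2 ≥60 mmHg).
- Reading B (PaO2 measured off oxygen): stable = V and off oxygen and PaO2 ≥60 mmHg.

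For a home-oxygen patient, both readings give: stable = V and oxygen need equal to the pre-admission need. I take the vital-sign limits to apply there as well.

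**The failure components.** Severe respiratory failure values = not intubated, PaO2/FiO2 <200 mmHg and respiratory rate ≥30/min. New ventilation = invasive ventilation not present at baseline.

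**Example patients.** The values are chosen for illustration. All have temperature 37.0 °C, heart rate 95/min, systolic pressure 120 mmHg and respiratory rate 32/min, so V is met.

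1. New oxygen or non-invasive ventilation, PaO2 70 mmHg, FiO2 0.60. Ratio = 70/0.60 = 117 mmHg. Reading A: stable. Reading B: not stable. Severe respiratory failure values: met. Under reading A the definitions overlap.
2. Newly intubated, same gases. Reading A: stable. Reading B: not stable. Severe respiratory failure cannot apply, because it is limited to patients not intubated, but the new-ventilation component is met. Under reading A the definitions overlap by that route.
3. Home oxygen, need above the pre-admission level, same gases. Not stable under either reading, so no overlap.
4. Room air, PaO2 60 mmHg. Ratio = 60/0.21 = 286 mmHg. Stable under both readings, failure values not met, so no overlap.

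**Why reading B removes the overlap.** Without home oxygen, a stable patient under B breathes room air, so the ratio is at least 60/0.21 = 286 mmHg and cannot fall below 200. Under A no such bound exists. At FiO2 0.60, any PaO2 below 200 × 0.60 = 120 mmHg gives a ratio below 200, and the respiratory rate is not checked.

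**Effect on the date.** Every patient-day that is stable under B is also stable under A, so the date under A is never later than under B. If a patient first meets V on day a while on new oxygen, and first meets V off oxygen with PaO2 ≥60 mmHg on day b, the two readings differ by b − a days.

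**Persistence.** One set of values after 72 h does not establish failure, because the severe respiratory failure component requires persistence. This does not remove the overlap: under A a patient who keeps these values is stable on each of those days.

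**The case against.** The strongest reply is that reading B is what was meant. The home-oxygen sentence makes sense as a relaxation for people who cannot come off oxygen. If being on oxygen simply waived the test, home-oxygen patients would face a stricter rule than newly hypoxaemic ones. The article also attributes the definition to a guideline, which may settle the matter. Much of this stands: B is plausible and probably the more coherent reading. But the printed grammar is conditional, the guideline is not reproduced, and the article gives the definition in full, so sites and analysts have to apply the words as they stand.

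A reader might be tempted to go further. The documents do not support these extensions:

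- *That any ventilated patient can meet the severe respiratory failure criterion while stable.* Intubated patients are excluded from it. For invasive ventilation the clash is with the new-ventilation component only, and a patient already ventilated at baseline does not meet that one either.
- *That oxygenation is tested only in patients off oxygen.* Home-oxygen patients have their own test.
- *That a single reading suffices, that pressure on a vasopressor counts, or that death and failure are mishandled as competing events.* The article is silent on these, and a condensed article may leave them to the full protocol or analysis plan. The wording "vital signs stable for > 24 h" belongs to a different endpoint, length of hospital stay, and shows nothing about this one.
- *That a difference between arms would reflect supportive care.* Both arms are treated under the same guidelines and the control arm receives placebo. The article gives no mechanism by which such care would differ by arm.

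**Conclusion.** The point holds as a defect of wording in one secondary endpoint. On the literal reading, a non-intubated patient newly on oxygen or non-invasive ventilation can be dated as clinically stable while showing the values that the primary endpoint treats as failure if they persist after 72 h. A newly intubated patient can be stable while failing through new invasive ventilation. On the other reading this overlap is gone. The definition therefore admits two stability dates for the same patient, and the literal one is never the later.

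Its size cannot be put as a number of patients. The article gives neither the share on newly started oxygen nor how many of them would meet the three vital-sign limits on a given day. Multiplying an assumed share on oxygen by 198 would count everyone on oxygen, not those whose date is wrong. The conclusion does not depend on that share.

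The primary endpoint is not altered. The sample size rests on treatment failure alone ("we assumed a treatment failure rate of 30% in the placebo group and 10% in the adjunct TCM group over 28 days") and is unaffected.

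**What to change.** Reconcile Time to clinical stability with Primary outcome measure:

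- Reword the oxygen limb as PaO2 of at least 60 mmHg without supplemental oxygen or, in patients on home oxygen, return to the pre-admission need.
- State that a patient on newly started oxygen or ventilation, or currently meeting a treatment failure criterion, is not counted as stable.

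This changes how an outcome is classified, not how anyone is treated. No further conditions are needed to remove the contradiction.

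The cost is small. Clinical status and vital signs are already reassessed every 24 h, and the present definitions already require sites to know whether a patient is on supplemental oxygen or intubated. Recruitment had begun, with 16 of 198 patients enrolled at submission, so the clarification should be dated and applied in the same way to patients already enrolled. The downside is that, compared with the literal reading, stability will be reached somewhat later and by fewer patients.

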##### Length of hospital stay

The time to the earliest possible hospital discharge (days) is based on objective criteria (able to take food, liquids, and drugs orally; vital signs stable for > 24 h; recovered from CAP-related worsening of mental status; and no evidence of an acute serious CAP-related comorbidity that necessitates hospitalization). This endpoint will minimize any potential bias due to extended hospitalization for non-disease-specific reasons (a request from the patient or their relatives, lack of adequate home care, inability to transfer to a nursing home, or lack of assurance about compliance with treatment) [13].

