#### Statistical analysis

A descriptive statistical analysis will be performed for all study variables. We will calculate the mean, median, and standard deviation for quantitative variables, and the absolute and relative frequency for qualitative variables. We will use SPSS 19.0 (SPSS Inc., Chicago, Illinois, United States) to analyze the data statistically. An intention-to-treat analysis will be applied using the last observation carried forward method for missing data. Analysis of covariance with the baseline as the covariate will be used to assess differences in treatment outcomes between the two groups at each of the time points. To correct for an inflated risk of type 1 errors, multiple comparison procedures suggested by Ludbrook et al. [14] will be used for the outcome measure by using it as a covariate in the statistical analysis. A data safety monitoring board has been established to assess the progress of the trial, particularly the safety endpoints.

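### The endpoint called length of hospital stay, like time to clinical stability, is a time to recovery that patients who die first never reach, and the stated LOCF/ANCOVA analysis does not suit it

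*Protocol article*

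**What the plan says.** Under Length of hospital stay, the endpoint is given as follows: "The time to the earliest possible hospital discharge (days) is based on objective criteria". The criteria describe recovery: "able to take food, liquids, and drugs orally; vital signs stable for > 24 h; recovered from CAP-related worsening of mental status", together with absence of a serious acute complication of the pneumonia. The stated purpose is to remove non-medical delay: "This endpoint will minimize any potential bias due to extended hospitalization for non-disease-specific reasons". Actual discharge is a separate matter, since Study protocol says "The time of discharge is not determined by the study investigators, but chosen by the treating physician team". Time to clinical stability is likewise the time until a set of recovery thresholds is met.

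The Statistical analysis section gives means, medians and standard deviations for quantitative variables, then "An intention-to-treat analysis will be applied using the last observation carried forward method for missing data" and "Analysis of covariance with the baseline as the covariate will be used to assess differences in treatment outcomes between the two groups", at each time point. No other method is stated for the secondary endpoints.

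The Discussion part of the Abstract expects that the combination "will reduce treatment failure, time to clinical stability, length hospital of stays, and in-hospital mortality". Death counts as failure in the primary endpoint and is recorded as a separate secondary outcome. Neither section links it to the two recovery times.

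**The concern.** Both endpoints are times to a good event. A patient who dies before that event has no observed time and never will have one, so this is not ordinary missing data. The article describes mortality in severe pneumonia as high and hypothesises that the arms will differ in it, so the number of patients without a value may differ by arm.

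The stated methods do not deal with this. Time to readiness has no baseline measurement to serve as a covariate and no series of visits to analyse one by one. Nor does it have an earlier observation to carry forward; the nearest literal reading is the last day observed, which turns an early death into a short stay. Leaving such patients out gives a comparison of survivors, which randomisation no longer protects. Either way, a treatment that prevents deaths could look slower to bring patients to readiness or stability than it is.

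The label adds a smaller problem. Readers will take a result called length of hospital stay to mean days in hospital, which the endpoint does not measure.

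**Working it through.** The article gives no expected stay and no mortality rate, so there is no figure of its own to reproduce. Every input below is an assumption, chosen to show the mechanism.

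**Hand calculation.** Assume that every survivor in both arms is ready on day 14, that deaths occur on day 7, and that mortality is 20% in control and 10% in TCM. Recovery in survivors is then identical.

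- Death ends the stay: control 0.8 × 14 + 0.2 × 7 = 12.6 days; TCM 0.9 × 14 + 0.1 × 7 = 13.3 days. TCM looks 0.7 days slower.
- In general the shift is the mortality difference × (14 − day of death). It runs from 0.05 × (14 − 10) = 0.2 to 0.15 × (14 − 3) = 1.65 days.
- Survivors only: 14 versus 14, no shift. If the 10% rescued by TCM need 20 days, TCM survivors average (0.8 × 14 + 0.1 × 20) / 0.9 = 14.7 days, about 0.7 days slower.
- Deaths held at day 28: control 0.8 × 14 + 0.2 × 28 = 16.8; TCM 0.9 × 14 + 0.1 × 28 = 15.4. TCM looks 1.4 days faster.

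**Simulation.** 99 patients per arm, 400 runs per scenario. Readiness is log-normal with median 11 days, and death times are exponential with mean 8 days, capped at 28. Treatment has no effect on readiness in patients who would survive in either arm. Patients rescued by TCM have median readiness of 20 or 11 days. Each cell gives results for mortality of 10% vs 5%, 20% vs 10% and 30% vs 10%, in that order. Differences are TCM minus control in days; a rate ratio above 1 favours TCM.

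| Handling of death | Rescued: median 20 | Rescued: median 11 |
|---|---|---|
| Ends the stay (days) | +0.8, +1.3, +2.8 | +0.2, +0.4, +0.9 |
| Survivors only (days) | +0.6, +1.0, +2.0 | 0.0, −0.1, −0.1 |
| Censored at death (rate ratio) | 0.96, 0.95, 0.91 | 1.06, 1.12, 1.23 |
| Worst value, day 29 (days) | −0.3, −0.8, −1.7 | −0.9, −1.7, −3.4 |
| Kept as never ready to day 28 (rate ratio) | 1.09, 1.18, 1.41 | 1.19, 1.32, 1.74 |

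With equal mortality (20% in both arms) every difference lies within 0.04 days of zero and the rate ratios are 1.01. A real gain can outweigh the distortion without removing it: at 20% versus 10% with rescued median 20, a true 2-day shortening appears as −0.4 days when death ends the stay.

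**The case against.** The strongest reply is that the article sets no rule for deaths in these endpoints. Coding rules for secondary time-to-event endpoints usually belong to an analysis plan, which is not shown, so their absence is no fault. That is right as far as it goes, and the point does not rest on absence. It rests on what is stated: a missing-data rule and a baseline-adjusted comparison, both worded for outcomes in general, that do not fit a recovery time cut short by death.

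A reader might infer something stronger: that the definition itself makes the better arm look slower. The documents do not support this. They do not say that LOCF applies to deaths or to this endpoint, and the sign turns with the handling rule, as the table shows. Nor is the survivor-only bias automatic: it needs rescued patients to recover more slowly than the others. The figures of 12.6 and 13.3 apply only if death closes the stay, which the definition does not say. The problem is also confined to patients who die before readiness; some may meet the criteria and die later.

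Other parts of the reply stand. These are secondary endpoints, and deaths are visible in the primary endpoint and in the mortality outcome. The definition sits directly under its loose label and gives its reason, so the naming point is minor. Data collection says "hospital discharge is recommended if oral intake is feasible, vital signs have been stable for ≥24 h", against more than 24 hours in the endpoint, but that is a care recommendation set beside an outcome definition. The difference is not material for a measure counted in days.

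**Conclusion.** The point holds in conditional form. Time to discharge readiness and time to clinical stability cannot be reached by a patient who dies first, the trial hypothesises a difference in deaths, and the stated analysis does not suit such endpoints. The resulting bias could run against the better arm. On the assumed inputs it is 0.2 to 2.8 days if death ends the stay. In a survivor-only comparison it is 0.6 to 2.0 days when rescued patients recover slowly, and about zero when they do not. It disappears if mortality is equal and reverses under worst-value or never-reached coding. No direction can be claimed from the documents alone. That the sign depends on a choice still open is a reason to fix the choice before results are known. The mislabelling is a valid but minor correction.

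**What to change.** For both endpoints, replace LOCF and ANCOVA in Statistical analysis with a time-to-event analysis through day 28. Treat death before readiness or stability as a competing event, or equivalently for this purpose keep the patient in the risk set as never reaching the event. Plain censoring at death is not a substitute, since its direction in the table depends on how fast rescued patients recover. Report the proportion ready or stable at day 28 in each arm. Change the label of the first endpoint to *time to discharge readiness* wherever it appears.

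The cost is small: endpoint wording and a coding rule, with no change to treatment or sample size. Trial status reports only 16 of 198 patients recruited at submission. There are two downsides. Results appear as cumulative incidence or a rate ratio rather than mean days, and that ratio reflects survival as well as speed of recovery, so it should be read beside mortality. The date of death must also be available; the article implies this through its daily inpatient reassessment and mortality recording but does not state it.
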